### 8.1.3 Missing data

Missing data will not be imputed in the primary analysis as the statistical methods for handling missing data rely on untestable assumptions. If individual frequencies are lacking from the audiometric data, we will average the whole of the available registered frequencies to determine PTA. Baseline measurements of those lost to follow-up will be included for the linear mixed model analysis. Since there will be no data from the 2-year control, and therefore no measured difference, these will not affect the results of our t-test. Our goal is to minimize the amount of missing data to ensure the quality of our study.

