### **Number of participants**

The calculation of the number of participants was performed by the statistician. The number depends on which factors which are to be analyzed and which statistical method will be used. We are interested in determining differences in effect of treatment in disfavor of the GP-group, but a better result in this group would be optimal in regards to the clinical implications (performing therefore a two sided test. No difference between groups is also a possibility and of interest (equivalence study). With a focus on the likeness between groups it is especially important to avoid falsely concluding “no effect” (type II error), which implies that we want a high power for the test for difference between groups, minimum 90%, preferably up to 95%.

The primary end-point is hearing, which is measured in dB (continuous variable). We examine changes in average hearing in the frequencies 0,25-4,0 kHz between 2 timepoints. The smallest clinically relevant change in hearing is 5dB. With an expected bettering of 10dB in the one group and 5dB in the other group (absolute diff. 5dB), and estimated standard deviation of 10dB in each group, we would with a significance of 5% need 85 (105) participants in each group to determine a difference with 90% (95%) power. To account for skew from the normal distribution, at least 15% should be added (increase to 98 or 131 in each group) and an additional 20% for drop-outs. A minimum of at least 118(157) participants in each group would be required. To maintain power in a model where we account for study center (random factor), and other clinical or demographic factors, the number must be increased (by at least 10 cases per variable. The total is now increased from 314 to 400, 200 participants in each group due to multiple participating hospitals.

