### **Preoperative examinations and measurements**

1. Self report form where audiograph and other health care personell at the audiological center/outpatient clinic enter the guardians' answers into a database («Web-CRF»). Information about ear complaints, subjective hearing and sociodemographic background questions, operation form and questionnaires regarding quality of life "OM 8-30", "PedsQL" and "SDQ".
2. Hearing testing, including puretone audiometry (0.25-4.0 kHz) (20) and speech audiometry (21). Should the child due to age or othe reasons be unable to cooperate with these tests, other test methods may be used, for example TEOAE (transient otoacoustic emissions)(22). Speech audiometry is performed using child lists, one syllable words, two syllable words or three word utterances or speed test three word utterances (23).
3. Tympanometry (pressure measurement)(24).

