## 5. Trial methods

### 5.1 Trial design

This is a multicenter randomized non-inferiority study involving six centers in Norway and organized through St. Olavs Hospital, Trondheim, Norway. Patients were included through Gjøvik hospital, Stavanger University Hospital, hospitals in Ålesund and Molde as well as a private practice in Kristiansund. An initial assessment of eligibility was performed through the out-patient ENT clinic upon further referral for operative implantation of tympanostomy tube(s). The surgical procedure was performed at one of the aforementioned hospitals.

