## 5.4 Statistical framework

### 5.4.1 Hypothesis test

Primary outcomes will be determined by measuring the change in the average of measured frequencies between 500Hz and 4kHz between baseline and control 2 years after the operative implantation of tympanostomy tubes. The null hypothesis is that controls performed by the GP lead to poorer PTA results 2 years after implantation of tympanostomy tubes compared to those performed within the specialist health care system. The alternative hypothesis will be that the mean change in PTA of patients controlled by their GP is not inferior to the PTA of patients controlled in the specialist health care system.

The test will be performed at the two-sided 5% significance level. A difference between the two groups will be claimed if the null hypothesis is rejected (p-value less than 5%). Superiority of controls within the specialist health care system will be claimed if the two-sided p-value in the test comparing the change from baseline is less than 5% and if the effect goes in favor of controls performed within the specialist health care system.

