# 8. Analysis

## 8.1 Analysis of the primary efficacy endpoint

### 8.1.1 Pure tone average (PTA)

The primary outcome will be the mean change in PTA from baseline between those patients controlled by their general practitioner and those controlled through the specialist health care system. PTA will be measured by taking the mean of the hearing thresholds in dB measured at 500Hz, 1kHz, 2kHz and 4kHz using pure tone audiometry.

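### SAP 8.1.3 lets a child's baseline and 2-year PTA come from different frequencies, so a change can appear in the primary variable when hearing has not changed

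*Combined protocol and SAP*

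**What the plan says.** SAP 8.1.1 fixes the primary variable: "PTA will be measured by taking the mean of the hearing thresholds in dB measured at 500Hz, 1kHz, 2kHz and 4kHz". SAP 5.4.1 describes it more loosely, as the change in the "average of measured frequencies between 500Hz and 4kHz".

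SAP 8.1.3 declines to impute in the primary analysis because methods for missing data depend on assumptions that cannot be tested. For audiograms that lack single frequencies it then says "we will average the whole of the available registered frequencies to determine PTA". It gives no minimum number of frequencies, no matching between visits and no sensitivity analysis.

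The PTA derived in this way feeds both analyses in SAP 8.1.2: the linear mixed model (LMM) with levels for baseline, post-ENT and post-GP, and the t-test of change. SAP 6.3 lists a complete case set, but does not say whether complete means all four frequencies and does not tie the set to the primary analysis.

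Three other statements bear on the size of the problem:
- The 5 dB margin in SAP 5.3 concerns the difference between group means.
- The protocol (Design and procedure) randomizes after the operation, so the baseline audiogram precedes allocation.
- SAP 5.5 blinds the audiographers to allocation.

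**The concern.** A child's thresholds usually differ between frequencies. If two visits are averaged over different subsets, the difference between the two PTA values mixes any real change with the shape of the audiogram. Followed as written, one threshold at one visit can be set against four at the other.

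The rule is also an imputation in all but name. Averaging the remaining thresholds gives the same result as filling each missing one with the mean of those observed, so it assumes a flat audiogram. That sits badly in a section that rejects imputation for its assumptions.

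Three things could suffer. Artefacts of varying size add noise to the primary variable. If 2-year audiograms are incomplete more often in one arm, they bias the comparison. Even with balanced arms, each arm's own mean change can be distorted, and so can the subgroup results in SAP 8.2 if incomplete audiograms cluster by age or by severity of hearing loss.

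**Working it through.** **1. The plan's own figure.** Inputs from SAP 5.3: difference 5 dB, SD 10 dB, two-sided 5%, power 95%. By normal approximation, n = 2 × (1.960 + 1.645)² × 10² / 5² = 104 per group; the t-based calculation gives 104.9, that is 105, as stated. A non-inferiority calculation (margin 5 dB, true difference 0, one-sided 2.5%) also gives 104.

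**2. The hidden imputation.** Let k of the four thresholds be observed, with mean m. Filling the other 4 − k with m gives [k·m + (4 − k)·m] / 4 = m, which is what 8.1.3 computes.

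**3. Size in one child with no true change.** The audiogram shapes are assumed, since the documents give none.
- Thresholds 30/30/20/20 dB at both visits. Baseline from 0.5 and 1 kHz only: (30 + 30)/2 = 30 dB. Full 2-year PTA: (30 + 30 + 20 + 20)/4 = 25 dB. Spurious gain: 5 dB.
- More generally, if the lower pair lies s dB from the upper pair, the artefact is s/2: 2.5, 5 and 7.5 dB for s = 5, 10 and 15.
- Largest artefact when one visit is complete and the audiogram slopes in equal steps:

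| Span across the four frequencies | 1 missing | 2 missing | 3 missing |
|---|---|---|---|
| 0 dB (flat) | 0 | 0 | 0 |
| 10 dB | 1.7 dB | 3.3 dB | 5.0 dB |
| 20 dB | 3.3 dB | 6.7 dB | 10.0 dB |

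- With one frequency missing at one visit only, the artefact is a quarter of the gap between that threshold and the mean of the other three. Reaching 5 dB needs a gap of 4 × 5 = 20 dB.

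**4. Size between arms.** Bias in the comparison of mean change = shift per affected child × difference between arms in the share affected.
- 5 dB shift: 0 dB if shares are equal; 5 × 0.10 = 0.5 dB at 10 points; 5 × 0.20 = 1.0 dB at 20 points; 5 dB only at 100 points.
- 10 dB shift: 10 × 0.50 = 5 dB, so a 50-point imbalance is needed.

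**5. Size in precision.** If a share p of children carries an artefact of s dB of mixed sign, unrelated to true change, the SD becomes √(100 + p·s²). Power at 105 per group is Φ(5 / (SD × √(2/105)) − 1.96).
- No artefact: SD 10, power about 95%.
- p = 20%, s = 5: SD = √105 = 10.25, power 94.2%.
- p = 20%, s = 10: SD = √120 = 10.95, power 91.1%.

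**6. What different rules leave behind.** If both visits use the same frequencies, unchanged thresholds give exactly 0 dB. If at least three of four are required at each visit, without matching, the largest artefact for linear spans of 5, 10, 15 and 20 dB is 1.7, 3.3, 5.0 and 6.7 dB. With no minimum, as in 8.1.3, it is 5, 10, 15 and 20 dB.

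**The case against.** The strongest reply is that the trial's design contains most of the damage. Short audiograms at baseline arise before allocation, so they produce no arm bias in expectation. Blinded audiographers limit differential incompleteness at 2 years. The LMM has one common baseline level, so a baseline artefact reaches the 2-year comparison only partly, through the within-child correlation. All of this stands, and it is why the trial-level size is small. It does not make the two PTA values of one child comparable.

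A reader might infer more from the rule than the documents support:
- **A bias as large as the margin.** The 5 dB in the illustration is one child's change, whereas the margin applies to the difference between group means. Step 4 shows how extreme an imbalance would be needed to reach it.
- **That short baseline audiograms are likely.** The protocol (Preoperative examinations and measurements) says "Should the child due to age or othe reasons be unable to cooperate with these tests, other test methods may be used". That concerns replacing the test, not partial audiograms, and the lower age limit was chosen so that hearing could be tested. Partial audiograms are possible, but no rate is given.
- **That 0.25 kHz would enter the average.** The protocol (Number of participants) says "We examine changes in average hearing in the frequencies 0,25-4,0 kHz between 2 timepoints", so that threshold may be on record. But SAP 8.1.1 and 5.4.1 both start at 500 Hz, and the natural reading of 8.1.3 is what is registered within that set.

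The change of frequency range between protocol and SAP, and which ear or ears PTA refers to, are separate questions and do not bear on this rule.

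**Conclusion.** The concern holds as a defect in a stated rule. Nothing in SAP 5.4.1, 6.3, 8.1.1 or 8.1.2 prevents a child's baseline and 2-year PTA from resting on different frequencies, and followed literally the rule gives a primary variable that is not the same quantity at both visits.

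The likely consequence for the main comparison is small. Precision falls slightly, from about 95% power to 94.2% if 20% of children carry a mixed-sign 5 dB artefact. Arm-level bias is 0 if affected shares are equal and 0.5-1.0 dB if they differ by 10-20 points at 5 dB each, which is 10-20% of the margin. These figures rest on assumed audiogram shapes and assumed shares of incomplete records, since the documents give neither. If audiograms are flat, or the same frequencies are missing at both visits, a child with unchanged hearing shows no artefact. The point is worth correcting because the correction is cheap, not because the trial's conclusion is likely to turn on it.

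**What to change.** In SAP 8.1.3:
1. Limit PTA explicitly to 0.5, 1, 2 and 4 kHz.
2. For children with both visits, compute PTA at both visits from the frequencies registered at both, and use these values in the t-test and in the LMM. Matching only the change score would leave the LMM untouched, and a three-of-four minimum alone would leave the artefacts in step 6. Say how a child with no frequency in common is handled.
3. As an alternative to item 2, fit the LMM to the frequency-level thresholds with frequency as a fixed factor. A random term for visit within child should then be added, because thresholds from one audiogram are correlated.
4. Report the number of incomplete audiograms by arm and visit.
5. Add a sensitivity analysis in children with all four frequencies at both visits. The complete case set in SAP 6.3 could be defined this way.

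The cost is SAP wording and slightly more derivation code. Under matching, some registered thresholds go unused. No new data are needed.

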## 8.2 Subgroup analyses

Subgroup analysis of the primary endpoint will be conducted for age, gender and severity of hearing loss at inclusion. The groups will be divided into thirds for analysis. Both the complete case set, and the two randomized groups will be divided into thirds according to level of hearing loss or age before subsequent analysis.

## 9. Safety analyses

Complications after implantation of ventilation tubes often occur outside of the standard controls. The current model refers the patient to their GP who can then refer the patient further to an ENT department should it be indicated. No changes to this practice were implemented.

## 10. Statistical software

All statistical analysis will be performed using Stata 18.0 MP (Stata corp. 2023. Stata statistical software: Release 18. College station, TX: Stata Corp LLC.) and R version 4.3.1 (R Core Team, R: A language and environment for statistical computing. R Foundation for Statistical Computing, Vienna, Austria. URL <https://www.R-project.org/>).

